### Assessments

Measures will be taken at baseline and at 3, 6 and 12 months after baseline. The diagnostic interview (M.I.N.I.) at baseline will be conducted by telephone by trained interviewers. At 12 months follow-up the depression, anxiety and PTSD sections of the M.I.N.I. will be assessed again by telephone by an interviewer blinded to treatment allocation. All other assessments will be performed online via a link to the self-report questionnaires sent by e-mail. Table 2 provides an overview of the measures and their time of assessment.

**Table 2 Tab2:** Overview of measures

Variable	Instrument	T0^*^	T1^*^	T2^*^	T3^*^
*Measures taken from patient*					
Demographics (patient characteristics)		X			
Current and history of treatment		X			
Diagnosis of depression and comorbid disorders	M.I.N.I. 5.0	X			X
Depressive symptoms	PHQ-9	X	X	X	X
Depressive symptoms & severity	QIDS-SR-16	X	X	X	X
Health related well-being (QALY)	EQ-5D-5L	X	X	X	X
Health care uptake and productivity losses TIC-P	TIC-P	X	X	X	X
Sense of mastery	SOMS	X	X	X	X
Treatment preference		X			
Patient expectancy	CEQ	X			
Therapeutic alliance	WAI-SF-PT		X		
Technology alliance	WAI-Online Therapy^a^		X		
Client satisfaction with treatment	CSQ-8		X		
Satisfaction with the online program SUS	SUS^a^		X		
Possible negative side-effects	INEP			X	
*Measures taken from therapist*					
Therapeutic alliance	WAI-SF-TH^b^		X		
Satisfaction with the online program	SUS^c^		X		

^a^Offered to condition receiving blended treatment only

^b^Has to be completed for each patient. Offered at the same time point as T1 assessment of the patient

^c^Has to be completed once per therapist after completion of the first blended treatment

*T0 refers to baseline and T1, T2 and T3 to the 3, 6 and 12 month questionnaires

### Outcome measures

#### Primary outcome measure

The primary outcome measure is *symptoms of depression* as assessed with the Patient Health Questionnaire-9 (PHQ-9) [46]. The PHQ-9 is a nine-item mood module that can be used to screen and to diagnose patients with depressive disorders. The 9 items are each scored on a 0–3 scale, with the total score ranging from 0–27 and higher scores indicating more severe depression. The PHQ-9 has shown to have good psychometric properties [47, 48].

The Quick Inventory of Depressive Symptomatology Self-Report (QIDS-16-SR) is used in addition to the PHQ-9, because this measure is more often used (especially in specialised mental healthcare) and therefore makes better comparison with other studies possible. The QIDS assesses *depression severity* and consists of 16 items (each item scores 0–3, total range 0–48), with higher total scores being indicative of a higher severity of depressive symptoms. The QIDS includes symptom domains of MDD based on DSM-IV and Research Diagnostic Criteria (RDC). The QIDS has shown highly acceptable psychometric properties, with internal consistency of α = .86 [49]. The cut-off points of 6, 11, 16 and 21 represent the thresholds for mild, moderate, severe and very severe depression, respectively.

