#### Economic evaluation

We will perform an economic evaluation from societal perspective, conducting a cost-effectiveness analysis (CEA) and cost-utility analysis (CUA). The CEA will be based on treatment response, defined as a 50 % pre-post reduction of QIDS-SR depressive symptoms [49]. The CUA will be conducted using quality adjusted life years (QALYs) as a generic measure of health gains. Multiple imputation using chained equations (MICE) will be used to impute missing cost and effect data. Predictive Mean Matching will be used to account for the skewed distribution of costs [70]. Variables that will be included in the multiple imputation model are variables related to missingness, variables related to costs and effects at 12 months of follow-up and all variables included in the analysis model. The number of imputations will be increased until the fraction of missing information (FMI) is 5 % or less [70]. The completed datasets will be analysed separately and pooled using Rubin’s rules [71].

Multilevel analyses with adjustment for mental health care institution will be done to estimate differences in costs and effects between bCBT and TAU while correcting for potential effect modifiers and confounders. Incremental cost-effectiveness ratios (ICERs) will be calculated by dividing the difference in costs by the difference in effects. Bias-corrected and accelerated bootstrapping with 5000 replications will be used to estimate statistical uncertainty. Bootstrapped cost-effect pairs will be plotted on cost-effectiveness planes (CE planes) to visualize the uncertainty surrounding the ICERs. Moreover, for decision-making purposes cost-effectiveness acceptability curves will be estimated showing the probability that bCBT is cost-effective in comparison with TAU at a range of different ceiling ratios. Finally, to test the robustness of our findings, sensitivity analyses will be performed. First, the economic evaluation will be conducted from a healthcare perspective. Secondly, a per protocol analysis will be done in which only participants completing the bCBT treatment protocol will be included.

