#### Clinical evaluation

Independent *t*-tests and *χ*2-tests will be used to estimate between-group differences in demographics and pre-treatment measures at baseline. Outcomes on continuous outcome variables at T1, T2 and T3 will be analysed via mixed-model analyses, with participants as random effects, and time (T1-T3), group (bCBT vs. TAU) and time x group as fixed effects, with baseline scores as a single covariate. To assess the magnitude of treatment effects, Cohen’s *d* effect sizes [72] for each time point will be calculated by dividing MM parameter estimates of fixed effects at each post-treatment assessment by the pooled standard deviation of baseline scores. Effect sizes under 0.2 are deemed to be small, 0.5 to be moderate and 0.8 to be large [72].

Differences in response and remission rates, as well as adherence rates will be examined using *t*-tests and *χ*2-tests. In addition, moderator analysis will be conducted for demographic variables such as gender, age, educational level, partner status, employment status, as well as treatment and patient characteristics.

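### The stated QIDS total range (0–48) and the severity cut-offs beside it (6/11/16/21) appear to come from different scoring rules; one verified rule should be stated and used throughout

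*Protocol article*

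**What the plan says.** All statements are in the protocol article.

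- **Scoring (Primary outcome measure).** The QIDS "consists of 16 items (each item scores 0–3, total range 0–48". No other way of forming the total is given.
- **Thresholds (same paragraph).** "The cut-off points of 6, 11, 16 and 21 represent the thresholds for mild, moderate, severe and very severe depression, respectively".
- **Content (same paragraph).** "The QIDS includes symptom domains of MDD based on DSM-IV and Research Diagnostic Criteria (RDC"). The number of domains and the way items map to them are not given.
- **Role.** The abstract names the QIDS alongside the PHQ-9 for the primary outcome. The Primary outcome measure section names the PHQ-9 as the primary measure and adds the QIDS for comparability with other studies.
- **Use in the cost-effectiveness analysis (Planned statistical analyses, Economic evaluation).** "The CEA will be based on treatment response, defined as a 50 % pre-post reduction of QIDS-SR depressive symptoms".
- **Response and remission (Clinical evaluation).** "Differences in response and remission rates, as well as adherence rates will be examined using" *t*-tests and χ² tests. No scale or threshold is given there for either rate.

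**The concern.** A severity classification has meaning only for the total on which it was set. Here the total is described as the sum of 16 items, yet all four thresholds lie in the lower 44% of that scale, and more than half of the possible scores fall in the top category. That pattern suggests a range taken from one way of scoring and cut-offs taken from another.

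The matter is more than descriptive because the QIDS supplies the response measure of the cost-effectiveness analysis, which is part of the primary objective. The item sum is also the only scoring rule the article gives, so anyone programming from the article would add up 16 items. If the instrument's own total is formed differently, three things could change: the severity bands, any remission rate based on the QIDS, and response status in the cost-effectiveness analysis. The results would also not be comparable with studies that use the instrument's own scoring, which is the article's reason for including the QIDS.

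**Working it through.** **1. Reproduce the stated range.** Inputs from Primary outcome measure: 16 items, each with a maximum of 3. The maximum sum is 16 × 3 = 48. The range 0–48 is arithmetically correct for a plain sum.

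**2. Place the cut-offs on that range.**

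| Band | Scores on 0–48 | Number of scores | Share of the 49 scores |
|---|---|---|---|
| Below mild | 0–5 | 6 | 12% |
| Mild | 6–10 | 5 | 10% |
| Moderate | 11–15 | 5 | 10% |
| Severe | 16–20 | 5 | 10% |
| Very severe | 21–48 | 28 | 57% |

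- Very severe starts at 21/48 = 44% of the maximum, an average item score of 21/16 = 1.3 out of 3.
- A 1 on every item gives 16 × 1 = 16, which is the severe threshold.

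This step uses only the article's own figures.

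**3. A possible explanation (assumption, not in the article).** Suppose the total is built from nine domains scored 0–3, so that the maximum is 9 × 3 = 27. The bands are then 0–5, 6–10, 11–15, 16–20 and 21–27, holding 6, 5, 5, 5 and 7 scores. The top band holds 7/28 = 25% of the scores and starts at 21/27 = 78% of the maximum. If each domain takes its highest item, a 1 on every item gives 9, which is mild rather than severe. The even spacing makes this explanation plausible but does not prove it. The only 0–27 range in the article belongs to the PHQ-9 ("with the total score ranging from 0–27 and higher scores indicating more severe depression").

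**4. Does the 50% response depend on the scoring?** If two totals differ only by a constant factor *c*, then *c*·T₁ ≤ 0.5·*c*·T₀ exactly when T₁ ≤ 0.5·T₀, so response status is unchanged. Item sum against domain total is not such a rescaling. A symptom covered by several items counts several times in the sum and once in the domain total. A patient whose worst sleep item stays the same while the other sleep items improve gains credit under the sum and none under a highest-item rule.

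**5. Illustrative size, under assumptions.** A simulation compared the 16-item sum with an assumed domain total: highest of 4 sleep items + highest of 4 appetite/weight items + highest of 2 psychomotor items + 6 single items (4 + 4 + 2 + 6 = 16 items, 3 + 6 = 9 domains).

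- Items were cut from a normal latent severity at −0.2, 0.5 and 1.2, with loadings of 0.5, 0.65 or 0.8.
- Latent means at baseline and follow-up were 0.6 and 0, 0.9 and 0, or 0.9 and −0.4, with a between-time correlation of 0.6.
- Each of the nine scenarios had 100,000 patients.

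| Quantity | Range over the nine scenarios |
|---|---|
| Patients in a different severity band, baseline | 46–68% |
| Patients in a different severity band, follow-up | 39–61% |
| Follow-up score below 6, plain sum minus domain total | 4 to 6 percentage points lower |
| 50% response rate, plain sum minus domain total | 4 to 8 percentage points higher |
| Patients whose response status changes | 6–12% |

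These sizes apply only if the data really are summed over 16 items and the instrument's own total resembles the assumed one.

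**6. What is not affected.** The sample size rests on Cohen's *d*. For the Dutch trial (margin 0.4, one-sided 5%, power 80%), n per arm = 2 × (1.645 + 0.842)²/0.4² = 77.3, rounded up to 78, or 156 in total as stated. For the European study (margin 0.2, two-sided 95% interval, power 90%), n per arm = 2 × (1.960 + 1.282)²/0.2² = 525.5, rounded up to 526, or 1052 as stated. Neither uses the QIDS range. Eligibility uses the M.I.N.I. and the PHQ-9, and stratification is by centre.

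**The case against.** The strongest reply is that the article contains no arithmetic error: 16 × 3 is 48, all four cut-offs lie within 0–48, and severity bands need not be of equal width. No analysis in the article is stated to use the cut-offs, so the sentence may be a slip of description with correct scoring behind it.

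Much of this stands, and it rules out several stronger conclusions that a reader might draw:

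- *That the cut-offs are shown to belong to a 0–27 QIDS total.* The article gives no such QIDS range, no number of domains and no domain rule.
- *That range and cut-offs are logically incompatible.* They fit badly, but nothing in the article makes it impossible to apply both to one score.
- *That remission will be misclassified.* Remission has no stated scale or threshold. A score below 6 is only one possible definition.
- *That the cost-effectiveness response is mis-scored because of the cut-offs.* A 50% reduction uses neither the cut-offs nor the maximum. It changes only if the data are actually summed over 16 items and the instrument's own total is formed differently.
- *That the primary analysis is at risk.* The methods text makes the PHQ-9 the primary measure, despite the abstract's wording.

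The reply does not remove the point itself. This is not a detail left to a fuller document: the article chose to state a scoring rule and a set of thresholds, and by its own figures the lowest non-zero answer on every item counts as severe depression. That rule is also the only one given for the outcome that drives the cost-effectiveness analysis.

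**Conclusion.** The point holds as a mismatch between a stated scoring rule and its stated thresholds. On the article's figures alone, very severe begins at 44% of the maximum and covers 28 of 49 scores. The two statements appear to come from different scoring rules, and a domain-based total is a plausible explanation still to be verified.

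The consequences are conditional. If the items are summed as written and the instrument is scored by domain, then under the assumed structure roughly 40–70% of patients would fall in a different severity band and 6–12% would change response status. If the 0–48 range is only a slip of description, no result changes and the correction is editorial. The article does not show which of these applies. The correction is worth making, but it does not bear on the PHQ-9 comparison or on the sample size.

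**What to change.** 1. Verify the QIDS-SR-16 scoring rule against the instrument's scoring manual.
2. Correct the stated range so that it matches the cut-offs, and say in one sentence how the total is formed.
3. Use that one total for severity, response, any QIDS-based remission rate and the cost-effectiveness analysis.
4. Check the scoring syntax of the online questionnaire for plain summing of the 16 items, and recompute totals if it is found.

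The cost is one corrected sentence and one check of syntax. The questionnaire is completed online item by item, so provided the item responses are stored, totals can be recomputed without new data collection.

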#### Secondary outcome measures

*A diagnosis of depression* will be assessed with section A and B of the *MINI International Neuropsychiatric Interview* (M.I.N.I.) version 5.0, a structured diagnostic interview based on the Diagnostic and Statistical Manual of Mental Disorders (DSM-IV) and on International Classification of Diseases (ICD-10) criteria [37]. In comparison with the patient-rated version of the SCID, the M.I.N.I. achieved a good Kappa score of 0.84 with a sensitivity of 0.96 and a specificity of 0.88 in diagnosing Major Depressive Disorder (MDD) [50].

The full M.I.N.I., with exception of section M (Anorexia Nervosa), N (Bulimia nervosa), and P (Antisocial personality disorder), will be conducted at baseline (T0) to determine lifetime and current depression, as well as current comorbid psychiatric. At 12 month follow-up (T3), the depression, anxiety and PTSD sections of the M.I.N.I. will be assessed again, covering the past 12 months.

*Demographic variables* including age, sex, ethnicity, marital status, educational level and employment status, as well as *history of treatment* for mental health problems will be assessed at baseline. In addition, patients will be asked about *treatment preference*, indicating which treatment alternative they prefer (bCBT or TAU) before being allocated to one of the two conditions.

*Patients’ expectancy of treatment* will be assessed after randomisation with the Credibility and Expectancy Questionnaire (CEQ). This questionnaire consists of six items measuring expectancies toward the therapy and the credibility of treatment options. The items are scored on one of two scales, one 9-point Likert scale ranging from 0 (not at all) to 9 (absolutely) or a continuous scale ranging from 0 % (not at all) to 100 % (absolutely). The sum score on credibility and expectancy can vary between 3 and 27, with higher scores being indicative of more positive attitudes. Both factors (credibility and expectancy) have shown to be stable across different populations, with high internal consistency within each factor [51].

*Locus of control* will be assessed with the 5-item version of the Sense of Mastery Scale [52], with proven good reliability [53]. Questions are scored on a Likert-scale ranging from 1 (‘totally disagree’) to 5 (‘totally agree’). The total score ranges from 5 to 25, with higher scores being indicative of a higher degree of perceived control. The Sense of Mastery Scale will be administered at all time points (T0-T3) to assess changes in locus of control.

*Patient’s satisfaction with the treatment* will be assessed with Client Satisfaction Questionnaire (CSQ-8), used to measure global patient satisfaction [54]. The questionnaire consists of 8 items that are measures on a 4-points scale. Total scores range from 8 to 32, with higher scores being indicative of higher levels of satisfaction. The CSQ-8 has high internal consistency of α = .93 [55].

*Satisfaction with the online platform* will be evaluated with the System Usability Scale (SUS), a simple 10-item questionnaire giving a global view of subjective assessments of usability of a technology system [56]. All items are measured on a 5-point Likert scale ranging from ‘strongly disagree’ to ‘strongly agree’. Total SUS scores have a range from 0–100. The questionnaire was found to be reliable and robust [57]. The SUS has to be completed by patients receiving bCBT only, and once per therapist three months after starting with their first blended treatment.

The *therapeutic alliance* between therapists and patient will be assessed with the short version of the Working Alliance Inventory (WAI-SF) [58], Dutch version [59]. The WAI-SF is a 12-item self-report questionnaire with responses on a 5-point Likert scale ranging from’never or rarely’ to ‘very often’. The questionnaire covers three dimensions of working alliance: 1) therapeutic goals, 2) tasks, and 3) bond. The subscales have shown to have good internal consistencies (α > .80). Both the patient and the therapist version of the questionnaire will be administered at T1, to determine the quality of the therapeutic alliance.

The *alliance between the patient and technologies* will be assessed with an adapted version of the WAI: the Working Alliance Inventory – Online Therapy, developed by Labpsitec (Labority of Psychology and Technology). The items address goals and tasks agreement with the online treatment program, and not with the therapist.

To assess possible *negative side-effects of the treatment*, the Inventory of Negative Effects of Psychotherapy (INEP) [60] will be administered at T2 (6 months after baseline). The version used in this study consists of 15 items, assessing a range of common changes participants experienced in line with their therapy, concerning their social and work environment. The following domains are covered: negative interpersonal changes, negative effects in an intimate relationship, family/friends, perceived dependence from therapist, stigmatisation. All items are rated on a 4-point Likert scale. For each item, respondents also state whether they attribute the adverse effects on the therapy or on other circumstances. Only item scores of those negative effects that were attributed on the therapy are added to the total score. Higher total scores indicate more negative effects. The INEP shows an internal consistency of α = 0.85 [60]. For the use in this study, the questionnaire was translated by the forwards-backwards method, i.e. the questionnaire was first translated from English into Dutch by two persons who reached consensus by discussion. Next, the questionnaire was translated back to English and was compared with the original questionnaire.

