### Inclusion and exclusion criteria

In order to be eligible, participants must be ≥ 18 years old, have a primary diagnosis of Major Depressive Disorder according to DSM-IV criteria as confirmed with the MINI International Neuropsychiatric Interview (M.I.N.I) [37], and have a score above 5 on the Patient Health Questionnaire (PHQ-9) [38]. Participants will be excluded if meeting any of the following criteria: 1) having acute risk of suicide, assessed clinically by trained interviewers with the M.I.N.I.; 2) having serious psychiatric co-morbidity (e.g. bipolar disorder, psychotic illness or substance dependence) that requires alternative treatment, primary to the treatment of MDD; 3) participating in other psychological treatment for depression, parallel to the intervention treatment of the study; 4) insufficient comprehension of the spoken and written Dutch language; 5) not having access to a computer or tablet with internet; 6) not willing to carry an Android smartphone during the treatment period (made available by the research team when they do not have an Android smartphone themselves); 6) not willing to be randomly assigned to one of the two treatment groups, bCBT or TAU.

For applicants that are at high risk for suicide, relevant information and telephone numbers are provided and therapists are notified such that standardised procedures within the participating mental healthcare centres can be followed. When stabilised, the patient can still potentially be eligible to participate.

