### Randomisation and blinding

Randomisation will take place at an individual level stratified by mental healthcare centre. The allocation will be conducted centrally at the VU Amsterdam by an independent team of researchers which is not involved in the trial. A computerised random number generator [39] is used to produce the allocation scheme with an allocation ratio 1:1. Subjects will be randomised into two groups: bCBT or TAU. The allocation is concealed, researchers and clinicians will be unknown to the randomisation scheme. Blinding for the treatment is not possible as it will be clear to both therapists and patients when the treatment is blended or not. However, the assessor conducting the M.I.N.I. at follow-up will be blinded to treatment status. The flowchart of the study is presented in Fig. 1, according to CONSORT guidelines [40].

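### The 12-month M.I.N.I. window opens at about baseline, so a depression diagnosis scored on it would be positive for nearly everyone in both arms

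*Protocol article*

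**What the plan says.** All places are in the protocol article.

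- **Entry (Inclusion and exclusion criteria).** Participants must "have a primary diagnosis of Major Depressive Disorder according to DSM-IV criteria as confirmed with the MINI International Neuropsychiatric Interview".
- **Timing (Assessments).** "Measures will be taken at baseline and at 3, 6 and 12 months after baseline". Table 2 lists the M.I.N.I. at T0 and T3 only.
- **Outcome (Secondary outcome measures).** The first entry is a diagnosis of depression, which "will be assessed with section A and B of the" M.I.N.I. At baseline the interview is used "to determine lifetime and current depression". For T3 the section gives one time frame: "the depression, anxiety and PTSD sections of the M.I.N.I. will be assessed again, covering the past 12 months".
- **Blinding (Randomisation and blinding).** "Blinding for the treatment is not possible as it will be clear to both therapists and patients". However, "the assessor conducting the M.I.N.I. at follow-up will be blinded to treatment status".
- **Other measures (Assessments).** Apart from the M.I.N.I., "All other assessments will be performed online via a link to the self-report questionnaires sent by e-mail".

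**The concern.** An outcome at 12 months should show where patients stand after treatment. The window stated for T3 reaches back to about the day they entered. Treatment starts after inclusion, preferably within two weeks, and the blended course lasts 19 to 20 weeks. So up to about 22 of the 52 weeks in the window lie before or during blended treatment. A patient who was well by month 6 and stayed well has still had MDD in the past 12 months.

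Patients and therapists know the allocation, and the other depression measures are self-report. The T3 interview is the one place where someone unaware of allocation judges whether depression is present. If that judgement is scored over a window that contains the qualifying episode, it is nearly constant, and the trial loses most of what the interview could say about treatment effect.

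**Working it through.** **1. The plan's own figure.** The article gives no figure for the M.I.N.I. outcome, so the check starts from the sample size. With a margin of 0.4 SD, no true difference, one-sided 5% and 80% power, n per arm = 2 × (1.645 + 0.842)² / 0.4² = 77.3. This rounds up to 78, or 156 in total, as stated. The steps below use 78 per arm without dropout.

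**2. Expected positive rate.** The article gives a sensitivity of 0.96 and a specificity of 0.88 for MDD. If a share q truly has MDD in the period that is scored, the expected M.I.N.I.-positive rate is

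0.96q + 0.12(1 − q) = 0.12 + 0.84q.

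**3. The 12-month window, every entry episode counted.** By eligibility q = 1 in both arms, so the rate is 0.96 in each and the expected difference is 0.

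**4. Current status at the interview.** Assume true current MDD of 30% in one arm and 50% in the other.

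- 0.12 + 0.84 × 0.30 = 37.2%
- 0.12 + 0.84 × 0.50 = 54.0%
- Difference: 16.8 points

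Approximate power at two-sided 5% is Φ((Δ − 1.96·s0)/s1), where s0 is the pooled and s1 the unpooled standard error. It is about 56%.

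**5. If only part of the entry episodes counts.** The baseline interview precedes randomisation, so a strict 12-month window could open shortly after it. Let w be the share of entry episodes counted in the window. Then q = w + (1 − w) × current rate, and the difference shrinks to (1 − w) × 16.8 points.

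| Share counted (w) | Expected positive | Difference | Approx. power |
|---|---|---|---|
| 100% | 96.0% vs 96.0% | 0 | none beyond type I error |
| 95% | 93.1% vs 93.9% | 0.8 points | 4% |
| 90% | 90.1% vs 91.8% | 1.7 points | 5.5% |
| 80% | 84.2% vs 87.6% | 3.4 points | 9% |
| 50% | 66.6% vs 75.0% | 8.4 points | 21% |
| Current status only | 37.2% vs 54.0% | 16.8 points | 56% |

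The power formula counts rejections in one direction only, so it can fall slightly below 5%.

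**6. Other assumed rates.** With 40% vs 60% and 20% vs 40%, current-status power is 56% and 59%, and the window dilutes the difference in the same way. With 30% vs 40%, current-status power is only about 19%. Current status is therefore no guarantee of power, but its difference can move with treatment.

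**7. Room and precision.** If at least 95% are positive in each arm, the arms can differ by at most 5 points. The 95% confidence half-width at 95% positive is 1.96 × √(2 × 0.95 × 0.05 / 78) = 6.8 points, more than the room available. At 50% positive the half-width is 15.7 points, but differences can then run over a far wider range.

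**The case against.** The strongest reply is that the sentence describes a recall period and is not a scoring rule. At baseline the same interview separates present from past episodes. On a natural reading, the 12-month period replaces the lifetime look-back for the follow-up year and current status is still noted. The article never defines the outcome as any MDD in the past 12 months, and a fuller document may fix the coding. This stands in part: the text does not exclude recording current MDD, and if that is what is scored, the arms can be compared. But the window is something the article states, not something it leaves out. It names the current time frame at baseline and only the 12-month window at T3.

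Three stronger readings are tempting and are not supported.

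- **That the trial's only blinded outcome cannot separate the arms.** The same blinded interview covers anxiety and PTSD. Neither is an entry criterion, so their 12-month rates are diluted by baseline cases but not fixed near 100%.
- **That equal rates would count as evidence of non-inferiority.** The 0.4 margin belongs to depressive symptoms. No margin or non-inferiority test is attached to the M.I.N.I., and the article does not give it the task of confirming the PHQ-9. Near-identical rates of about 96% might simply be recognised as uninformative.
- **That a blinded interview would settle the question of self-report bias.** Only the assessor is blinded. The answers come from patients who know their treatment, so even a well-defined interview outcome is a partial check.

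**Conclusion.** The point holds conditionally. If the T3 diagnosis of depression is scored on the stated window, it will be positive for nearly all patients in both arms and will carry little or no information on treatment effect. The 96% figure rests on the article's sensitivity and on every entry episode being counted. The loss of contrast (16.8 points reduced to between 0 and 8.4) rests on assumed current rates, on a counted share between 100% and 50%, and on full follow-up of 78 per arm.

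The reach is limited to one secondary outcome at one time point. The PHQ-9 primary analysis and the sample size do not depend on it. It still deserves correction, because it wastes the only depression measure with a blinded assessor.

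**What to change.** In Secondary outcome measures, state that the T3 depression outcome is current M.I.N.I. MDD at the time of the interview, recorded by the blinded assessor and using the current-episode questions applied at baseline. Report the 12-month window separately and only as a description of course, or replace it with relapse in a window that starts after treatment ends.

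The cost is a wording change and the scoring of current-episode questions in an interview already planned. No extra contact or participants are needed. If interviewers already record current status, it is enough to name it as the outcome. If they do not, their instructions should change as soon as possible, because current status that was not recorded at T3 cannot be recovered afterwards. The article reports that recruitment was still under way.
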